# One-layer versus two-layer duct-to-mucosa pancreaticojejunostomy after pancreaticoduodenectomy: study protocol for a randomized controlled trial

**DOI:** 10.1186/s13063-016-1517-8

**Published:** 2016-08-17

**Keywords:** Postoperative pancreatic fistula, Pancreaticojejunostomy, Duct-to-mucosa, Pancreaticoduodenectomy

## Abstract

**Background:**

Although various pancreaticojejunal duct-to-mucosa anastomosis methods have been developed to reduce the postoperative risks of pancreaticoduodenectomy, pancreatic fistula remains the most serious complication with a high incident rate. The aim of this study is to compare the safety and effectiveness of one-layer and two-layer duct-to-mucosa pancreaticojejunostomy in patients undergoing pancreaticoduodenectomy.

**Methods/design:**

In this study, adult patients who sign consent forms will be recruited and scheduled for elective pancreaticoduodenectomy. One hundred and fourteen patients will be included and randomized before pancreaticojejunal reconstruction and after resection of the lesion from the pancreatic or periampullary region. The primary efficacy endpoint is the incident rate of postoperative pancreatic fistula. Statistical analysis will be based on the intention-to-treat population. Patients will be followed up for 3 months by monitoring for complications and other adverse events.

**Discussion:**

This prospective, single-center, randomized, single-blinded, two-group parallel trial is designed to compare one-layer with two-layer duct-to-mucosa anastomosis for pancreaticojejunal anastomosis during elective pancreaticoduodenectomy.

**Trial registration:**

Clinical Trials.gov: NCT02511951. Registered on 29 July 2015.

**Electronic supplementary material:**

The online version of this article (doi:10.1186/s13063-016-1517-8) contains supplementary material, which is available to authorized users.

## Background

To date, pancreaticoduodenectomy (PD) has been regarded as the only potentially curative treatment for pancreatic head and periampullary tumors, including tumors in the ampullary region, distal biliary duct, and periampullary duodenum [1]. A retrospective study in which 1000 cases were recruited over the past three decades showed that PD has become an effective treatment to reduce hospital mortality [2]. Mortality has been reduced to less than 5 %, but the morbidity remains at 30–50 % [2, 3]. Postoperative pancreatic fistula (POPF) is one of the most frequent and ominous complications after PD, and its occurrence reportedly ranges from 2–40 % [4, 5]. Severe POPF prolongs hospital stay and requires the use of specific treatments, such as the use of antibiotics, nutritional support, endoscopy, interventional radiology, and/or reoperation, etc. [6]. POPF risk is increased by many factors including pancreatic texture, main pancreatic duct diameter, and pancreaticojejunal (PJ) anastomotic technique [7–9]. Among these factors, only anastomotic technique can be improved. According to the International Study Group of Pancreatic Surgery (ISGPS) definition, POPF exists if the drainage of any measurable volume of fluid containing amylase exceeds three times the normal serum value on or after postoperative day (POD) 3 [10].

Several anastomotic surgical techniques have been developed to reduce the incidence of pancreatic fistula in recent decades, including the duct-to-mucosa method, pancreaticogastrostomy, Peng’s binding method, and the “end-to-end” or “end-to-side” invaginated method. Among these techniques, the conventional duct-to-mucosa method remains the most popular anastomosis due to its advantages. The size of the pancreatic remnant is not limited; moreover, the jejunal lumen and pancreatic remnant lead to easier anastomosis [11–14].

Compared with two-layer duct-to-mucosa anastomosis, the novel one-layer duct-to-mucosa PJ anastomosis method has been reported to be efficient at reducing POPF occurrence [15, 16]. However, the two cited retrospective studies might lead to selection bias. Because this evidence is insufficient, we will conduct a randomized controlled trial to verify the superiority of one-layer duct-to-mucosa PJ anastomosis after PD over the two-layer technique.

## Methods/design

### Study aim

The aim of this study is to compare the effect of two duct-to-mucosa PJ anastomotic methods for PD by assessing factors that are related to mortality or morbidity, including postoperative pancreatic fistula rate, biliary leakage, postpancreatectomy hemorrhage, and anastomosis time.

### Patient involvement

Sample size calculation is based on the primary endpoint: POPF rate. According to published data, an assumed absolute risk of 22 % difference in POPF occurrence is the appropriate basis for the calculation assuming 4.5 % POPF in the one-layer technique group and 26.7 % in the two-layer technique group [15, 16]. This calculation yields a total of 51 patients in each group, which assures a power of 90 % at a two-sided level of significance of 5 % (NCSS and PASS 11 (NCSS Statistical Software, Kaysville, UT, USA)). Assuming an expected withdrawal rate of 10 % during the trial, 12 additional patients will be included and randomized; therefore, the total sample size required is *n* = 114 patients (Fig. 1) (Additional files 1 and 2).

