#### Randomization

To achieve intervention groups with comparable known and unknown risk factors, randomization will be performed. The randomization number will be generated using computer-generated random numbers with an allocation ratio of 1:1 (an equal probability of assignment to either group). All patients will be randomized using consecutively numbered opaque envelopes that will have been sealed by the investigators. The envelopes will be opened before PJ reconstruction and after resection of the lesion from the pancreatic or periampullary region.

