### Statistical analysis

The two-sided null hypothesis for the primary endpoint measurement states that both study interventions will lead to a similar POPF occurrence rate; the alternative hypothesis is that one intervention will perform better than the other. The null hypothesis will be tested by analyzing the covariance while adjusting for pancreatic texture (soft or hard) and main pancreatic duct diameter (<3 mm or ≥3 mm). A binary logistic regression will be applied to compare the POPF occurrence rates between the groups after adjusting for other factors. Background characteristics and surgical outcome measures will be compared using chi-squared or Fisher’s exact tests for categorical data and two-tailed *t* tests or nonparametric Mann–Whitney *U* tests for continuous variables. Categorical data will be presented as frequencies and group percentages, and continuous variables will be expressed as the means and standard deviations. The homogeneity of two groups will be described by comparison of the demographic data and baseline values. All analyses will be performed on an ITT basis [17]. For the ITT analysis, the data will be processed for all trial patients in their randomized groups. A *P* value < 0.05 will be considered statistically significant. All statistical calculations will be performed using SPSS10.0 (SPSS, Chicago, IL, USA).

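### The 90% power holds for an unadjusted two-proportion test, but the analysis section does not fix the deciding primary test; a Wald test from the planned logistic model would have about 80% at 51 per arm

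*Protocol article*

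**What the plan says.** The protocol article, Patient involvement, bases the sample size on the POPF rate alone. It assumes 4.5% with the one-layer and 26.7% with the two-layer technique, "at a two-sided level of significance of 5"%, and concludes: "This calculation yields a total of 51 patients in each group, which assures a power of" 90%. It names the software but no test, and mentions no covariates. Twelve patients are added for 10% withdrawal, giving 114 in total (57 per arm at the 1:1 ratio given under Randomization).

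The Statistical analysis section describes a different kind of analysis. It first says that the null hypothesis for the primary endpoint is tested by analysis of covariance, adjusting for pancreatic texture (soft or hard) and main duct diameter (below 3 mm or not). It then says: "A binary logistic regression will be applied to compare the POPF occurrence rates between the groups", with adjustment for other factors. Chi-squared and Fisher's exact tests are listed there for background characteristics and surgical outcome measures. The section does not say which of the two adjusted analyses decides the primary question, or which test of the logistic treatment coefficient is meant.

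**The concern.** The power statement and the analysis statement concern the same endpoint but different procedures. That is often harmless. Here it may not be, because the assumed one-layer rate is very low: about two fistulas are expected in that arm. With so few events, tests from one and the same logistic model can disagree sharply. With no event in an arm, the maximum-likelihood odds ratio is infinite and the Wald P value, the one usually read from the coefficient table, is close to 1 however large the difference. If the deciding test is not fixed, that choice could settle significance after the data are seen, in the very samples where the one-layer technique has done best.

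**Working it through.** **Inputs.** From Patient involvement: p1 = 0.045, p2 = 0.267, two-sided alpha 0.05, power 90%, 51 per group, 114 in total. From Randomization: 1:1, so 57 per arm if everyone is analysed. The protocol gives no prevalence or effect for the covariates.

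**1. The plan's own figure.** With unpooled variance:

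n = (1.960 + 1.2816)² × (0.045×0.955 + 0.267×0.733) / 0.222² = 50.9, so 51 per group. This matches.

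The pooled-variance formula gives 54.03, so 55; with continuity correction, 63. The withdrawal allowance also reproduces: 102 / 0.9 = 113.3, so 114.

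**2. Expected events at 51 per arm.**
- One-layer: 51 × 0.045 = 2.3.
- Two-layer: 51 × 0.267 = 13.6.
- Total: about 16, or roughly 5 per term in a model with treatment, texture and duct diameter.

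**3. Chance of no fistula in the one-layer arm.**
- 51 per arm: 0.955^51 = 9.6%.
- 57 per arm: 0.955^57 = 7.2%.

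**4. Exact power without covariates**, by full enumeration of the two binomials. Wald counts zero-event samples as non-significant.

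| Test | 51 per arm | 57 per arm |
|---|---|---|
| Wald test of the log odds ratio | 80.1% | 85.1% |
| Fisher's exact | 84.9% | 89.6% |
| Pearson chi-squared | 90.9% | 93.9% |
| Unpooled z | 92.2% | 94.7% |
| Likelihood ratio (logistic) | 92.1% | 94.7% |

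**5. Where the Wald loss arises.** At 51 per arm the gap to the likelihood-ratio test is 92.1 − 80.1 = 12.0 points. If the zero-event samples counted as rejections, the Wald figure would be 80.1 + 9.6 = 89.6% (from unrounded values), so about 9.6 of the 12.0 points come from those samples. The likelihood-ratio and Pearson tests each reject in more than 99.9% of them. As an illustration, 0/51 against 14/51 gives a Wald P of 0.995 and a Fisher P of 0.00004.

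**6. Adjusted analyses**, by simulation (4000 runs per scenario). Assumptions, since the protocol gives no figures: each binary covariate has 50% prevalence and an odds ratio between 1 and 5.

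| Test | 51 per arm | 57 per arm |
|---|---|---|
| Logistic, Wald | 79–84% | 84–88% |
| Logistic, likelihood ratio | 92–95% | 94–97% |
| Linear analysis of covariance on the 0/1 outcome | 91–94% | 93–96% |

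In a separate simulation with both covariate odds ratios set to 3, Firth penalised logistic regression had 91.5% and the stratified CMH test 91.7% at 51 per arm.

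**The case against.** The strongest reply is that the protocol never names the Wald test. The logistic model it does name, tested by likelihood ratio, has 92.1% power at 51 per arm and rejects in almost every zero-event sample. Analysis of covariance is mentioned first and also exceeds 90%. Sizing a trial on an unadjusted comparison and then adjusting for prognostic factors is common practice, and adjustment by itself does not erode the power here. The choice of coefficient test is also a detail that an analysis plan may settle.

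Most of this stands, and it rules out two stronger readings. A reader might infer that the planned logistic regression has only 80% power. The document does not support that: 80% belongs to one unnamed way of testing the coefficient. A reader might also infer that the sample size is miscalculated. It is not: 51 reproduces exactly, and exact Pearson power at that size is 90.9%, which supersedes the pooled formula's approximate 55.

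What the reply does not remove is the conflict in the printed text. The article states a power guarantee and names two analyses for one binary endpoint without ranking them. One ordinary reading, the logistic P value from the coefficient table, misses the stated 90% even with all 114 patients analysed (about 85%, or 84–88% adjusted).

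**Conclusion.** The concern holds in a limited form. The 51 per group and 90% power are right for an unadjusted two-proportion test. The analysis section replaces that test with two adjusted analyses and leaves open which decides. If the decision rests on the Wald logistic test, power is about 80% rather than 90% at 51 per arm and about 85% at 57, mostly because of a 9.6% or 7.2% chance of no fistula in the one-layer arm. With the likelihood-ratio, penalised or CMH-type tests the shortfall disappears.

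The unadjusted figures are exact and rest only on the protocol's assumed rates. The adjusted ranges depend on assumed covariate prevalence and effects. Severity: should be fixed, not must be fixed, because the named model can deliver the promised power.

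**What to change.** In Statistical analysis, name one deciding primary test for the binary endpoint that holds up with sparse cells. Suitable choices are:
- Firth penalised logistic regression with a profile-likelihood P value and confidence interval, adjusted for texture and duct diameter;
- the likelihood-ratio test from the ordinary logistic model;
- a CMH test stratified by texture and duct diameter.

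Label the remaining analyses as supportive. With any of these the 90% statement can stand (about 92% at 51 per arm), and the sample-size paragraph needs only a phrase saying that it was based on an unadjusted two-proportion test.

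If a Wald test is kept as the deciding one, restate the power as about 80% at 51 per arm and about 85% at 57.

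The cost is a sentence or two and no extra patients. There are two small drawbacks. The unadjusted likelihood-ratio test is slightly liberal (size about 5.6% at the average event rate, (4.5 + 26.7)/2 = 15.6%). Firth regression would need a macro or software other than the SPSS version the protocol names.

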**Fig. 1 Fig1:**
[figure not shown]
Flow chart according to CONSORT

### Eligibility criteria

#### Inclusion criteria

Patients who meet the following criteria will be included in the study:Age 18–80 yearsElective pancreaticoduodenectomyProvision of informed consent.

#### Exclusion criteria

Patients who meet any of the following criteria will be excluded from the study:Patients with any severe cardiopulmonary disease: American Society of Anesthesiologists (ASA) classification or ejection fraction below 30 % that might prolong the postoperative hospital stayPrevious pancreatic operationImmunodeficiency, such as that observed under HIVEmergency operationPregnancy.

#### Withdrawal

Patients can withdraw from the trial at their own request or at the request of their legal representative at any time. Patients may be removed if, in the investigator’s opinion, continuation of the trail could be detrimental to the patient’s well-being or if a PD is not performed due to technical unresectability, metastatic disease, or other reasons. Every withdrawal will be recorded in the clinical report forms (CRFs) and in the patient’s medical case records. All examinations scheduled for the final trial day will be performed on all patients and documented. All data will be analyzed according to the intention-to-treat (ITT) principle [17].

#### Ethics, study registration, and consent

The final protocol has been approved by the Ethics Committee of the Second Affiliated Hospital of Anhui Medical University (approval number: KY201502). The trial protocol has also been registered in the protocol registration system at ClinicalTrials.gov (identifier: NCT02511951). All patients will be scheduled only after comprehensive information concerning the nature, scope, and possible consequences of the clinical trial has been provided to them in an understandable way by the investigator. Written informed consent for the study will be obtained from each patient before the operation. The study procedure, benefits, risks, and data management will be clarified in detail during the preoperative conversation.

## Trial interventions

### One-layer duct-to-mucosa PJ anastomosis

For the one-layer technique group, to create the posterior suturing layers, double needles with a 4–0 Prolene line (Ethicon, Shanghai, China) will be used; one side of the needles will be inserted from the posterior inner side of the pancreatic duct and out through the dorsal parenchyma of the pancreatic stump to the posterior surface of the pancreas at a point approximately 0.5 cm from the cut edge. The other side of the needles will be started from the inner side of the jejunum lumen, then pushed through the subserosa and seromuscular region, and out from the posterior surface of the bowel (Fig. 2). The anterior suturing layer will be treated in the same manner. An internal pancreatic duct stent will be inserted into the duct of the pancreatic remnant according to its size. Drain tubes will be placed anterior and posterior to the anastomosis (one each) when the anastomosis has been completed (Fig. 3).

**Fig. 2 Fig2:**
[figure not shown]
The procedure of end-to-side one-layer duct-to-mucosa PJ anastomosis: the posterior suturing layer

**Fig. 3 Fig3:**
[figure not shown]
The anterior suturing layer with duct-to-mucosa PJ anastomosis

### Two-layer duct-to-mucosa PJ anastomosis

For the two-layer continuous suture method, the same double needle and 4–0 Prolene line will be used. First, the region approximately 1.0 cm from the cutting edge of the pancreatic remnant will be freed; then, the posterior surface of the pancreatic remnant will be sutured to the seromuscular layer of the jejunum using the continuous suturing method (Fig. 4). The jejunum will be brought closer to the stump of the pancreas, and a hole of similar diameter to the main pancreatic duct will be made on the jejunum near the entrance of the main pancreatic duct. The posterior wall of the jejunum near the hole will be sutured to the posterior wall of the pancreatic duct using the continuous suturing method with Prolene line, and a suitable internal pancreatic duct stent will then be placed approximately 4–6 cm into the main duct (Fig. 5). The interior side of the jejunum and pancreas will be sutured using the same method. Then, the anterior surface of the pancreatic remnant and the seromuscular layer of the jejunum will be tightly sutured using the continuous method. Drain tubes will be managed as described above.

**Fig. 4 Fig4:**
[figure not shown]
The procedure of end-to-side two-layer duct-to-mucosa PJ anastomosis: the seromuscular layer

**Fig. 5 Fig5:**
[figure not shown]
The procedure of two-layer duct-to-mucosa PJ anastomosis: duct-to-mucosa layer

### Primary and secondary endpoints

#### Primary endpoint

The primary efficacy endpoint of the trial will be the POPF occurrence rate. POPF is defined by the International Study Group of Pancreatic Fistula (ISGPF) as any measurable volume of drain fluid that contains three times higher amylase content than the normal upper serum value, on or after POD 3. Amylase will be assessed on PODs 1, 3, 5, and 7. Three grades of POPF are determined according to clinical severity: A, B, and C [10].

#### Secondary endpoints

Secondary outcomes will be postoperative hospital stay, anastomosis time, postpancreatectomy hemorrhage, biliary leak, delayed gastric emptying, wound infection, intra-abdominal fluid collection or abscess, relaparotomy, and mortality. Existent ISGPS definitions will be used to ensure the comparability and generalizability of the results (Table 1). Postoperative complications will be graded based on severity according to the Clavien-Dindo definition [18] (Table 2).

**Table 1 Tab1:** Definition of secondary endpoints

Secondary endpoint	Definition and assessment of outcomes
Anastomosis time	Time from beginning to end of PJ anastomosis
Mortality	Death due to any cause until 90 days after the operation and the reason
Morbidity	Postoperative complications will be recorded until 90 days after operation. The severity of complications will be graded according to the Clavien-Dindo classification [18]
Postoperative hospital stay	Time from day of operation until discharge (days)
Postpancreatectomy hemorrhage	Evidence of blood loss from drains and/or nasogastric tube, based on ultrasonography, as defined by ISGPS [19]
Biliary leak	Bilirubin concentration in the drain fluid at least three times the serum bilirubin concentration as defined by International Study Group of Liver Surgery [20]
Delayed gastric emptying	Failure to resume solid diet with prolonged need for nasogastric tube as defined by ISGPS [21]
Intra-abdominal fluid collection	Collection of fluid measuring ≥3 cm associated with clinical or laboratory abnormalities
Wound infection	Surgical site infection associated with laparotomy that develops during the initial hospital stay
Pneumonia	Presence of a new infiltrate on chest X-ray, as well as following: body temperature >38 °C, abnormal elevation of white blood cells, or positive sputum, and requiring antibiotic treatment
Abdominal rupture	Dehiscence of abnormal closure with need for resuture of the laparotomy during the initial hospital stay

**Table 2 Tab2:** Complication grades according to the Clavien-Dindo classication scheme^a^

Grade	Definition
I	Any deviation from the normal postoperative course without the need for pharmacological treatment or surgical, endoscopic, and radiological intervention
II	Requiring pharmacological treatment with drugs other than those allowed for grade I complications
III	Requiring surgical, endoscopic, or radiological intervention
IIIa	Intervention not under general anesthesia
IIIb	Intervention under general anesthesia
IV	Life-threatening complication. Requiring intensive care unit management
IVa	Single organ dysfunction
IVb	Multi-organ dysfunction
V	Death of patient

^a^The Clavien-Dindo classification system is reported in detail elsewhere [18]

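### Wound infection and abdominal rupture are counted only until discharge, a time the technique may itself change; the resulting bias is avoidable and probably small

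*Protocol article*

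**What the plan says.** All of this is in the Protocol article, mostly under Secondary endpoints and in Table 1.

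- Wound infection: "Surgical site infection associated with laparotomy that develops during the initial hospital stay".
- Abdominal rupture: "Dehiscence of abnormal closure with need for resuture of the laparotomy during the initial hospital stay".
- Morbidity: "Postoperative complications will be recorded until 90 days after operation", graded by Clavien-Dindo.
- Mortality: "Death due to any cause until 90 days after the operation and the reason".
- Hospital stay is a compared outcome. The running-text list opens "Secondary outcomes will be postoperative hospital stay, anastomosis time, postpancreatectomy hemorrhage", and Table 1 measures stay from the operation to discharge.
- Follow-up, in the Abstract: "Patients will be followed up for 3 months by monitoring for complications and other adverse events". Table 3 schedules postoperative outcomes on postoperative days (POD) 1, 3, 7 and 90.

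The Background states that severe POPF lengthens the hospital stay. The sample size section assumes POPF rates of 4.5% (one-layer) and 26.7% (two-layer).

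Wound infection is in the running-text list of secondary outcomes. Abdominal rupture is defined in Table 1 but is not in that list. No reason is given for ending these two windows at discharge.

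**The concern.** A count of events is comparable between arms when every patient is observed for the same period, or when the period is unrelated to treatment. Here the period ends at discharge, which comes after randomization. On the protocol's own reasoning the technique can shift it: fewer fistulas, fewer prolonged stays, earlier discharge. Randomization does not balance a window that closes at a post-randomization outcome.

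The direction is predictable. The arm that goes home earlier is watched for fewer days and so shows fewer wound infections and ruptures, even if the true risk is the same. If the trial's hypothesis is right, that is the one-layer arm. A reader could then take part of a shorter observation period for a benefit on the wound.

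**Working it through.** **What the plan gives.** It states no wound-infection rate, onset time or length of stay, so there is no figure of its own to reproduce on this point. Two inputs come from the sample size section:

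- POPF rates of 4.5% and 26.7%, a difference of 26.7 − 4.5 = 22.2 percentage points.
- 114 patients in total, allocated 1:1, so 114 / 2 = 57 per arm.

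**Assumptions for the illustration (not in the documents).** The true risk is the same in both arms and does not depend on POPF: 10% by day 30, at constant hazard. Stay is 14 days without POPF and 28 days with POPF of any grade.

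**Step 1, hazard.** h = −ln(0.90) / 30 = 0.003512 per day.

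**Step 2, risk seen before discharge,** 1 − exp(−h × stay):

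- 14 days: 4.80%
- 28 days: 9.37%

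**Step 3, weight by the planned POPF rates:**

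- One-layer: 0.955 × 4.80% + 0.045 × 9.37% = 5.0%
- Two-layer: 0.733 × 4.80% + 0.267 × 9.37% = 6.0%

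The ratio is 0.83 and the difference about 1.0 percentage point. Per arm of 57 this is 2.9 against 3.4 events, a gap of about 0.6 event. A common fixed window gives a difference of zero under the same assumptions.

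**Step 4, whole-arm differences in stay.** Same hazard, with every patient in an arm given the same stay:

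| Stay (days) | Observed risk | Ratio | Events per 57 |
|---|---|---|---|
| 14 vs 18 | 4.80% vs 6.13% | 0.78 | 2.7 vs 3.5 |
| 10 vs 15 | 3.45% vs 5.13% | 0.67 | 2.0 vs 2.9 |

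These ratios look larger but need a strong premise. If POPF is the only route from technique to stay, a 4-day difference in mean stay requires 4 / 0.222 = 18 extra days for each additional POPF patient. A 5-day difference requires 5 / 0.222 = 22.5 days. Both sums let every grade of POPF prolong stay, while the Background says so only of severe POPF.

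**Step 5, earlier onset.** Now let onset be exponential with mean 7 to 14 days, scaled to a 90-day risk r of 10% to 20%. The share of events that has occurred by day t is F(t) = (1 − exp(−t/m)) / (1 − exp(−90/m)), where m is the mean onset. With the stays of 14 and 28 days, the spurious difference is r × 0.222 × [F(28) − F(14)].

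- Smallest (m = 7, r = 10%): 0.10 × 0.222 × (0.982 − 0.865) = 0.26 percentage points, or 0.15 event per 57.
- Largest (m = 14, r = 20%): 0.20 × 0.222 × (0.866 − 0.633) = 1.03 percentage points, or 0.59 event per 57.

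With whole-arm stays of 12 vs 16, 12 vs 20 or 14 vs 24 days, the same onset model gives 0.8 to 3.8 percentage points, or 0.5 to 2.2 events per 57. The top of that range needs a 10-day difference in mean stay, which is 10 / 0.222 = 45 extra days per additional POPF patient. It is best read as an outer bound.

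**The case against.** The strongest case against is that this is a legitimate and common choice. Counting in hospital restricts the endpoint to events that staff observe directly. Table 3 has no scheduled visit between POD 7 and POD 90, so a 90-day count would add events recalled weeks later. The effect in patients is small, every input to its size is assumed, and the primary endpoint is untouched. Because complications are recorded to day 90 anyway, a fixed-window count could be tabulated from data the trial will hold.

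Most of this stands. It limits the importance of the point but does not remove it. The plan already commits to recording complications to day 90, so recall at that visit is a weakness it has accepted for morbidity. Keeping the in-hospital count as a split preserves the directly observed figure. That the data will exist makes the fix cheap, but as written the named endpoint still stops at discharge.

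Two stronger readings are tempting and are not supported:

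- A reader might infer that Table 1 contradicts itself, because an infection after discharge counts as morbidity but not as wound infection. Morbidity is an aggregate over 90 days, and the two named events have their own explicit, narrower window. Different endpoints may have different windows.
- A reader might take a ratio such as 0.67 as the likely distortion. That rests on a whole-arm difference in stay that the documents do not give, and it amounts to about one event per arm.

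**Conclusion.** The point holds as an avoidable bias in a minor secondary endpoint. Wound infection carries it; abdominal rupture has the same definition but is not in the running-text list of secondary outcomes. The direction is clear: fewer counted events in the arm discharged earlier. The size is unknown and probably small. When the difference in stay is tied to the planned POPF rates, the illustrations give roughly 0.3 to 1.0 percentage point, under one event per arm of 57.

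These figures rest on assumed infection risk, onset pattern and stays, on a risk unrelated to POPF, and on any POPF prolonging stay. If only severe POPF does so, the effect is smaller. The mechanism itself needs only that the technique changes the length of stay. The primary endpoint is not affected.

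**What to change.** In the wound infection and abdominal rupture rows of Table 1, replace the limit to the initial stay with one fixed period for all patients. Ninety days is the natural choice, since it matches the Morbidity and Mortality rows and the last scheduled visit. Report the in-hospital count beside it as a descriptive split, so that directly observed events remain visible.

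The cost is two definition lines. No new visit is needed, because complications are already to be recorded to day 90. The downside is that events after discharge would rest partly on history taken at the POD 90 visit, and the report should say so.
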